### Statistical analyses

The analyses will be performed blinded. The groups are compared regarding primary and secondary outcomes using Chi-square/Fisher’s exact test for frequencies and Mann-Whitney test for continuous outcomes. Analyses will be conducted using intention-to-treat principles. A p-value < 0.05 is considered statistically significant. Subgroup analyses for determination of prognostic factors are done through logistic regression analyses.

The cost-effectiveness of the GSP-A will be estimated by comparing the incremental cost to the incremental effect of the two groups. The GSP-A is considered more cost-effective than standard care if it is less costly and more effective. If the GSP-A is more costly and more effective, the additional cost per abstainer has to be considered worth paying [44].

Data will be analysed using IBM SPSS v. 19 and Excel 2010.

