## Methods/Design

### Study design and setting

A randomised clinical multi-centre study will be conducted including adult (minimum 18 years) patients undergoing ankle fracture surgery and drinking 21 or more drinks (one drink equals 12 g ethanol) per week for at least 3 months before admission. Patients are consecutively recruited from multiple orthopaedic wards at university hospitals. The centres initially participating in the study are Bispebjerg/Frederiksberg, Hvidovre and Southern Jutland from Denmark, Lund from Sweden as well as Haukeland and Stavager from Norway.

Included patients will be randomly allocated to either the intervention group or control group (standard care). Patients in the intervention group will receive the GSP-A aimed at alcohol abstinence at the time of ankle fracture surgery and 6 weeks after. It includes a structured patient education programme and weekly interventions meetings initially at the orthopaedic ward and continued after discharge at the outpatient clinic (5 in total). Patients in the control group will receive standard care for patients with hazardous alcohol intake according to the clinical guidelines in the wards.

For both groups follow-up assessments will be conducted after 6 weeks and 3, 6, 9 and 12 months after surgery; see trial profile in Figure 1. The primary outcomes are postoperative complications requiring treatment, alcohol intake (abstinence and non-hazardous drinking) as well as cost-effectiveness. The effect of the GSP-A will be assessed comparing the outcome measures between the intervention and control group at each follow-up point.

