### Randomisation, allocation concealment and sequence generation

A computer-generated list of random numbers will be used for allocation of the patients. The randomisation sequence is created using www.sealedenvelope.com statistical software, and is stratified by centre with a 1:1 allocation using random block sizes. The list is generated by a researcher not otherwise involved in the project and prior to the commencement of recruitment. The allocation sequence will be concealed from the research staff enrolling and assessing participants in sequentially numbered, opaque, sealed and stapled envelops that are impermeable to intense light. Corresponding envelops will be opened only after the patients have given informed consent and it is time to allocate the intervention group.

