### Data collection

Baseline data will be collected for all included patients during admission in interviews: A detailed alcohol profile on intake over time (Timeline Follow-back [32]), ICD-10 criteria for alcohol dependency [33], test for alcohol use disorders (AUDIT-C [34]), alcohol withdrawal symptoms (CIWA-Ar [35]), breath test (ethanol during expiration), blood sampling for liver function (haemoglobin, alkaline phosphates, gamma-glyteryl-transferase, amino-transferases, bilirubine) and for alcohol markers (carbohydrate-deficient transferring, ethanol, phosphatidylethanol, mean cell volume, serum, EDTA–plasma and citrate-plasma); urine sampling for alcohol markers (ethyl glucuronide, ethyl sulphate, ethanol).

Furthermore, baseline characteristics regarding age and sex, socio-demographic factors, other lifestyle factors (smoking, overweight, risk of malnutrition and physical inactivity [36]), co-morbidity, self-rated ankle function, and self-evaluated health assessed in the SF-36 questionnaire [37] will be obtained for all patients.

During admission the following information will be collected from the medical records: AO-classification of the ankle fracture and surgical characteristics; ASA-score [31], operative procedure, antibiotics and thrombo-embolic prophylaxis, type of anaesthesia, blood loss, infusions, implants and surgical or anaesthetic problems. Besides, length of hospital stay, use of resources and medicines, discharge or transfer will be registered for all patients.

Follow-up visits will be conducted after 6 weeks, 3, 6, 9 and 12 months in the orthopaedic outpatient clinics. Patients will be evaluated on postoperative complications and second surgery, Olerud-Molander Ankle Score [38], dorsal plantar flexibility (after 3, 6, 9 and 12 months) and fracture status after 12 months confirmed by x-ray (satisfactory healing, secondary dislocation or non-union. Effect on alcohol intake will be assessed by Timeline Follow-back [32], alcohol withdrawal symptoms (CIWA-Ar [35]), breath test (ethanol during expiration) as well as blood sampling for liver function, alcohol markers and urine sampling for alcohol markers. Besides data on rehabilitation, readmissions, ED, general practitioners, specialist doctor, physiotherapist and occupational therapist, alcohol treatment services, nursing home, community nurse, home care, return to work and/or previous activity level, and use of medicines will be collected at all follow-up points.

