### Sample size

Sample size calculations are restricted by this being the first study evaluating the effect of alcohol cessation intervention in acute fracture surgery, and the number of patients needed differ depending on the outcome.

The effect on alcohol abstinence is based on the preoperative intensive alcohol interventions, which showed a very high effect above 90% in the intervention groups versus less than 10% in the control groups [16]. However, a more moderate effect is expected in acute fracture surgery with 50% abstainers in the GSP-A group after 6 weeks. This corresponds to a minimum of 2×12 patients.

Postoperative complication rates among ankle fracture patients were 30% for patients drinking at least 5 drinks per day versus 10% in patients without hazardous alcohol intake in a case-control study [42]. If similar complication rates after 6 weeks are expected in the control and GSP-A group respectively, a total maximum of 2×59 patients should be recruited over the 3 to 4 years inclusion period.

The number of patients for the cost-effectiveness analyses is based on the expected effect on the clinical outcomes [43].

All sample size calculations are based on a power of 80% and a risk of type 1 failure on 5%. Also to reduce differences between patient populations, each centre should include about 20 patients.

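### Randomisation is stratified by centre and baseline SF-36 and CIWA-Ar are collected, but the stated tests use neither; they stay valid but give up some precision

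*Protocol article*

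**What the plan says.** The section on randomisation, allocation concealment and sequence generation says that the allocation list "is stratified by centre with a 1:1 allocation using random block sizes". Study design and setting names the initial centres: "Bispebjerg/Frederiksberg, Hvidovre and Southern Jutland from Denmark, Lund from Sweden as well as Haukeland and Stavager from Norway". That makes six strata. The Sample size section adds that "each centre should include about 20 patients".

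Under Data collection, "self-evaluated health assessed in the SF-36 questionnaire [37] will be obtained for all patients" at baseline. CIWA-Ar is listed there both at baseline and at follow-up. SF-36 and the degree of withdrawal symptoms are secondary outcomes.

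The Statistical analyses section compares the groups on primary and secondary outcomes with Chi-square or Fisher's "exact test for frequencies and Mann-Whitney test for continuous outcomes". The only regression it names is logistic, and that is reserved for finding prognostic factors in subgroup analyses. Nowhere does the article describe a treatment comparison that is stratified by centre or adjusted for a baseline value.

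**The concern.** Stratified allocation balances the arms within each centre, so differences between centres largely drop out of the treatment contrast. A pooled test still counts those differences in its standard error. If complication or abstinence rates vary between centres, the standard error is too large and the test rejects less often than its nominal 5%. Likewise, when a score is measured before treatment and again afterwards, leaving out the first measurement leaves predictable variation in the error term.

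What is at stake is precision, in a trial of at most 2×59 patients whose recruitment has ended. Because the article names its tests, this is a stated choice and not a detail left to an analysis plan.

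**Working it through.** **Inputs from the protocol article:** six centres of about 20 patients, 1:1 within centre; complications 30% (control) v 10% (GSP-A); 80% power; 5% type 1 error (taken as two-sided, which the article does not state); 59 per arm.

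**Inputs not given, so assumed over a range:** the between-centre SD of the log-odds, and the correlation r between baseline and follow-up score.

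**Step 1: the plan's own figure.** Two proportions, unpooled variance:

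n per arm = [p₁(1−p₁) + p₂(1−p₂)] × (1.960 + 0.842)² / (p₁−p₂)² = (0.21 + 0.09) × 7.849 / 0.04 = 58.9, rounded up to 59.

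This reproduces 2×59. The figure is an unadjusted calculation with no centre term. Exact power of the uncorrected chi-square at 59 per arm is 80.5%.

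**Step 2: pooled chi-square v CMH by centre.** Simulation with 40,000 trials per row, six centres, 10 per arm in each, normal random centre effects on the logit scale, and average rates held at 30% v 10% (power) or 30% v 30% (type 1 error). The simulation error of a power figure is about √(0.8 × 0.2 / 40,000) = 0.2 points.

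| Centre log-odds SD (assumed) | Power, chi-square | Power, CMH | Gain (points) | Type 1 error, chi-square |
|---|---|---|---|---|
| 0 | 80.2% | 80.0% | −0.2 | 5.3% |
| 0.5 | 80.5% | 81.4% | 0.9 | 4.7% |
| 1.0 | 81.3% | 84.1% | 2.8 | 3.6% |
| 1.5 | 81.6% | 86.7% | 5.1 | 2.8% |

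The type 1 error of CMH stays between 4.8% and 5.0% throughout. To judge the scale: around a 30% rate, ±1 SD means centre rates of about 14% to 54% at SD 1.0.

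**Step 3: uneven centres.** With assumed centre sizes of 50, 30, 16, 10, 8 and 4 (118 in total), CMH v chi-square power is 79.4% v 80.4% at SD 0, 79.9% v 79.9% at SD 0.5, and 81.6% v 79.7% at SD 1.0.

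**Step 4: SF-36.** For a comparison of means, ANCOVA on the baseline score multiplies the variance by 1 − r². A comparison with 80% power unadjusted then has power Φ(2.802/√(1−r²) − 1.960).

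| r (assumed) | Variance factor 1 − r² | Power if 80% unadjusted |
|---|---|---|
| 0.3 | 0.91 | 84% |
| 0.5 | 0.75 | 90% |
| 0.7 | 0.51 | 97.5% |

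Complications, length of stay and time to return to work have no baseline value of their own, so this gain does not reach them.

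**The case against.** The strongest case on the other side is that nothing is broken. The design and the stated test agree: 2×59 comes from an unadjusted calculation, and chi-square keeps about 80% power in every row of Step 2. With little or moderate difference between centres, the gain on complications is under one point. The Strengths and limitations section warns that recruitment may vary between centres, and with uneven centres that do not differ CMH loses about a point. All of this stands, and it limits the weight of the point.

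Four stronger readings are tempting, and the article does not support them.

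- **That the stated tests are invalid.** When centres differ, the error is in the conservative direction, with type 1 error below 5%. At SD 0 chi-square shows 5.3%, which is the approximation in a small sample and has nothing to do with stratification.
- **That care is known to differ by centre.** The article says that control care follows ward guidelines. It does not say that these differ, so large centre effects remain an assumption.
- **That the trial loses a quarter of its information.** The factor 0.75 needs r = 0.5, concerns a secondary outcome, and compares ANCOVA with an unadjusted comparison of means, not with the Mann-Whitney test. The baseline is taken during an acute admission, so r is unknown.
- **That SF-36 will be compared as a raw follow-up score.** The article does not say whether the score or its change is tested, and that detail may sit in an analysis plan. The answer would not remove the point. With equal variances at both times, a change score has variance factor 2(1 − r), which is 1.4, 1.0 and 0.6 at r = 0.3, 0.5 and 0.7. ANCOVA is better in each case.

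**Conclusion.** The point holds in a modest form. The article fixes tests that ignore its own randomisation strata and baseline scores. Results from those tests can be relied on, but they are less precise than the collected data allow.

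For complications, the cost is about 0–1 power point if the centre log-odds SD is 0–0.5. It is about 3–5 points at SD 1.0–1.5, where the type 1 error of chi-square falls to about 3–4%. These figures assume six equal centres and the planned 30% v 10%. For SF-36 the variance reduction is 9%, 25% or 49% at r = 0.3, 0.5 or 0.7. The direction is certain for SF-36 whenever r is not negligible. For the primary outcome it depends on how much centres differ and how evenly they recruited, and the article gives neither.

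**What to change.** State in the analysis section or the analysis plan:

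- **Binary primary outcomes:** Cochran-Mantel-Haenszel test stratified by centre, with a stratified risk difference and its 95% confidence interval.
- **SF-36 and CIWA-Ar:** ANCOVA with the baseline score and centre as covariates.
- **Continuous outcomes without a baseline value, such as length of stay:** a centre-stratified rank test (van Elteren).
- **Sensitivity analyses:** the chi-square, Fisher and Mann-Whitney tests as now stated.

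No new data are needed. CMH is workable with about 20 patients per centre. It also avoids loading a model with covariates when only about 59 × 0.30 + 59 × 0.10 ≈ 24 complications are expected.

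There are two costs. One is a possible loss of about one power point if centres are very uneven and do not differ. The other is a late change of test: Project status says that inclusion has ended and the analysis of short-term outcomes is under way. The change and its reason should therefore be dated and recorded before the blinded analysis is opened. If any comparison by arm has already been seen, the stated tests should stay primary and the stratified or adjusted analyses should be reported as supporting.

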### Project status

Patient inclusion was finalised in 2014. A few patients are still in the follow-up process, and the analysis of short-term outcomes is still ongoing. The study is supposed to be completed by the end of 2015.

## Discussion

The overall aim of the Scand-Ankle project is to contribute to the development of evidence-based guidelines for perioperative alcohol cessation interventions, and this is the first study to evaluate the effect of a new comprehensive GSP-A on postoperative complications, alcohol intake and cost-effectiveness in acute fracture surgery.

A recent study shows that hazardous drinking patients with ankle fracture still have a very high complication rate (personal communications [name] et al.) similar to the rates used for the sample size calculation for this trial.

### Strengths and limitations

The randomised design provides evidence on the highest possible level regarding the effect of alcohol cessation intervention in acute fracture surgery. Blinding of patients and project staff is not possible or intended as the GSP-A includes patient education to support abstinence. However, evaluation of postoperative complications is performed blinded by an orthopaedic specialist unaware of the patients’ group allocation. Also, the statistical analyses are done blinded by an independent researcher.

Recruitment of patients to the trial is expected to be difficult, as the number needed to screen (NNS) to identify and include eligible patients may be very high. The NNS to get one eligible to accept participation in alcohol intervention studies varies from a few up to 70 patients [13]. The rates do not differ between RCTs and non-RCTs, or between brief and intensive alcohol intervention studies. Also, in a study on smoking cessation intervention in acute fracture surgery 61% of the eligible patients declined to participate [45]. Finally, recruitment rates may also vary between countries and/or centres.

### Perspectives

The study provides new knowledge about alcohol treatment and how to prevent alcohol-related postoperative complications as well as cost-effectiveness of these at the time of acute fracture surgery. From a clinical perspective this may help to improve the perioperative course. At the same time it will be necessary to address hazardous drinking among patients in acute fracture surgery, and thus also a need for systematic identification of alcohol intake, more detailed patient information as well as better education of staff. For the patients a shorter period of alcohol abstinence could be a positive experience and may also initiate a general reduction in hazardous drinking, which will be a benefit on long term. Also, the prospect of fewer complications is important from the patient perspective. For the society an optimised postoperative course, decreased use of health care resources and fewer sick days will induce immediate cost-savings, and in addition, fewer alcohol-related problems will also benefit society.

### Ethics approval and consent to participate

The Danish Scientific Ethical Committee System (CVK: 0908664), as well as the corresponding Ethical Committees in the Sweden (EPN Lund: 2009/9) and Norway (REK Vest: 2009/717), have all approved the project. The project has been approved by The Danish Data Protection Agency (2009-41-3741).

## Abbreviations

BI: Brief intervention
DIS: Disulfiram
ED: Emergency Department
NNS: Number needed to screen
GSP-A: Gold standard programme for alcohol cessation intervention
RCT: Randomised clinical trial
